**3.6.2 Secondary Study Aim #1 Outcomes**

**Specific Aim 2** tests the hypothesis that an OLP reduces symptoms severity of CRF and improves perceived wellbeing and quality of life for CSs compared to an observational control. To assess effect, we will administer the following measures to measure specific outcomes related to CRF:

- **FACT-F** is a 41-item questionnaire that assesses quality of life concerns pertinent to cancer patients. It has evidenced good internal consistency reliability and concurrent validity that measures the following domains:

Physical well-being (7 items)

Social/Family well-being (7 items)

Emotional well-being (6 items)

Functional well-being (7 items)

Fatigue (13 items)

- **Multidimensional Fatigue Symptom Inventory** (MFSI-SF 30) is an instrument that considers the multidimensional conceptualization of cancer-related fatigue beyond symptom severity and intensity. In terms of validity, correlations between the 5 subscales of the MFSI-SF (listed below) and 2 measures of fatigue have demonstrated excellent concurrent validity and correlations with a measure of physical well-being provided support for convergent validity.

Global Symptom Severity

Physical Health

Emotional Health

Mental Health

- **Fatigue Symptom Inventory (FSI)** assesses the frequency and severity of fatigue as well as its perceived disruptiveness. Frequency is measured as the number of days in the past week (0–7) respondents felt fatigued as well as the percentage of each day on average they felt fatigued (0 = none, 10 = entire day). Perceived severity is measured on 4 separate 11-point scales (0 = not at all fatigued, 10 = as fatigued as I could be) that assess most, least, and average. Perceived disruptiveness is measured on 7 separate 11-point scales (0 = no interference, 10 = extreme interference) that assess the degree to which fatigue in the past week was judged to interfere with general level of activity, ability to concentrate, relations with others, enjoyment of life, and mood. Interference ratings are also summed to yield a total disruptiveness score**.**
- **Medical Outcomes Study) (MOS SF-36**) is a set of generic, coherent, and easily administered quality-of-life measures. These measures are widely utilized by managed care organizations and by Medicare for routine monitoring and assessment of care outcomes in adult patients.

The estimated completion time for the questionnaires outlined above is 25 minutes.

**3.6.3 Supplementary Aim Outcomes**

**This supplementary aim** is intended to evaluate variances of COMTVal18Met genotype that may serve as potential biomarkers for placebo responders. Should significant OLP effects be obtained, we will evaluate whether variants of COMT Val18Met (met/met, met/val and val/val alleles) associate with placebo responsiveness.

**3.6.4 Primary Endpoint**

To evaluate the feasibility of recruiting and enrolling CSs into an OLP and the acceptability of CSs of an OLP for the treatment of CRF.

**3.6.5 Covariates**

We will analyze the following covariates to determine effects on outcomes:

- Age
- Sex
- Race
- Time Since Last Treatment

**3.7 Statistical Methods**

The statistical analysis will be conducted under the direction of [name]. This pilot study will provide us important information concerning the acceptability and feasibility of OLP for treating CRF. It will also provide information on study design, retention and outcomes assessment.

**Power Calculation**: Our sample size calculations were based on minimal assumptions. Hence for each outcome, our planned sample size calculations indicated that we would have power of 80% assuming a two-tailed two-sample t-test on the outcomes at day 21, Type 1 error rate of 0.05, we would need a sample size of 80 to detect an effect size of 0.64. Techniques such as ANCOVA or two–sample independent t-test comparing change scores would be powerful or require less sample size to detect the same effect size depending on the correlation between baseline and follow-up measures

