**3.0 INVESTIGATIONAL PLAN AND PROCEDURES**

**3.1 Study Design and Population**

We propose to conduct a pilot randomized-controlled, crossover trial to evaluate the feasibility, acceptability and effect of the open-label administration of placebo pills on CRF and associated psychosocial factors (e.g., emotional health, social health, quality of life, etc.) for cancer survivors (CSs) who have completed all cancer treatments yet continue to experience CRF. Additionally, in an exploratory manner, we propose to collect DNA saliva specimens that we intend to analyze in the future to identify potential biomarkers for predicting placebo responses.

To do this, we will use a 7-week, single site, two-parallel arm, randomized controlled crossover pilot study to determine the feasibility, acceptability and effects of an OLP on CSs who completed cancer treatments at least 6 months prior to enrollment in the study and report a fatigue score of 4 or greater on a 0-10 scale.

We will enroll 80 eligible CS participants who will be randomized into two groups of 40 (Group1 and Group2). In this crossover study, participants in Group1, will receive an OLP (placebo pill) for 21-days and Group2 (Observational Controls) will not. After a 1-week washout period, Group2 will receive the OLP for 21-days and Group1 (Observational Controls) will not (see Figure 1a: Study Design Schema).

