**Specific Aim 2:** We will test the hypothesis that an OLP intervention reduces symptoms severity of CRF and improves quality of life for CSs compared to an observational control. The primary analysis for this aim will consist of mixed models repeated measures analysis, such as repeated measures analysis of covariance. This will allow the investigators to properly test for the absence of a carryover effect as well as account for the fact that all patients will receive both treatments (i.e., this type of analysis allows each patient to serve as his/her own control).

**Supplementary Aim:** evaluates the presence or absence of the COMTVal18Met genotype as a correlate for improved fatigue conditions and quality of life. We will measure this using a logistic regression model to determine associations. In addition, we will calculate the odds ratio and corresponding 95% confidence intervals.

**Multiple Comparisons Tests (Post Hoc Test):** To account for multiple comparisons, we will apply a Bonferroni procedure and control the family-wise error rate at .05.

**Missing Data**: Data deemed missing at random (MAR) will be handled using multiple imputation techniques with the Bayesian based Markov-Chain Monte-Carlo (MCMC) method. In supplementary analysis, we will use independent t-tests and chi-square to compare completers versus dropouts.

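### The 80% power at effect size 0.64 is correct only at alpha 0.05 for each outcome with all 80 measured at Day 21; the Bonferroni rule and the retention benchmark in the same section are not reflected in it

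*Protocol*

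**What the plan says.** Section 3.7 (Power Calculation) opens with "Hence for each outcome, our planned sample size calculations indicated that we would have power of 80" percent, "assuming a two-tailed two-sample t-test on the outcomes at day 21", and concludes "Type 1 error rate of 0.05, we would need a sample size of 80 to detect an effect size of 0.64". It adds that ANCOVA or change scores would do better, depending on the correlation between baseline and follow-up.

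Section 3.1 enrols exactly that number: "We will enroll 80 eligible CS participants who will be randomized into two groups of 40".

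Four other statements bear on the figure:

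- Section 3.7, under a heading on multiple comparisons that carries the label post hoc: "To account for multiple comparisons, we will apply a Bonferroni procedure and control the family-wise error rate at .05". The number of comparisons is not given.
- Sections 3.6 and 3.6.2 measure the effect with four questionnaires, three of them described with several domains or dimensions. Hypothesis 2 in section 2.0 speaks of fatigue severity and quality of life. No score is named as the lead outcome for Aim 2.
- Section 3.7 (Acceptability) sets the retention benchmark at more than 75%, with no time point.
- Section 3.7 (Specific Aim 2) makes a repeated-measures mixed model over both crossover periods the primary analysis, including a test for carryover, and plans multiple imputation for data missing at random.

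**The concern.** The power sentence spends alpha 0.05 on every outcome and counts all 80 participants. The multiplicity rule limits the error over a family to .05, and the retention benchmark counts the trial as successful with little more than 60 participants. The sample size allows for neither.

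The effect of the multiplicity rule depends on how it is read. If it covers the Aim 2 outcomes, the power for each outcome is below the stated 80%. If it covers post hoc contrasts only, the outcomes are each tested at 0.05 and nothing controls the error across them.

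Aim 2 is the trial's only comparison of efficacy. A significant effect triggers the COMT genotype work, and section 1.0 expects the effect sizes to inform a larger trial. A null Day 21 comparison could be judged against power it does not have, or a single positive score among several against an error rate that was not kept.

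**Working it through.** **Inputs.** From the protocol: d = 0.64, two-sided two-sample t-test at Day 21, alpha 0.05, 40 per group, retention above 75%, Bonferroni at .05. Assumed: the number of tests K, because the protocol gives none. K = 4 is one score per questionnaire; K = 2 is one fatigue and one quality-of-life score. The loss case takes the boundary of the benchmark, 0.75 × 80 = 60 or 30 per group, and puts all loss before Day 21.

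**Method.** Power = P(T > t_crit), where T is noncentral t with 2n − 2 degrees of freedom and noncentrality d × √(n/2), and t_crit is the two-sided critical value at 0.05/K.

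- n = 40: noncentrality 0.64 × √20 = 2.862.
- n = 30: noncentrality 0.64 × √15 = 2.479.

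**The plan's own figure.** With n = 40 and alpha 0.05, t_crit = 1.991 and power = 80.7%. The effect detectable with 80% power is 0.634. The statement is arithmetically right on its own terms.

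**With the other rules applied (d = 0.64).**

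| Case | Alpha per test | t_crit (n = 40; 30) | Power, 40 per group | Power, 30 per group |
|---|---|---|---|---|
| No adjustment | 0.05 | 1.991; 2.002 | 80.7% | 68.4% |
| K = 2 | 0.025 | 2.286; 2.301 | 71.7% | 57.3% |
| K = 4 | 0.0125 | 2.557; 2.578 | 62.1% | 46.6% |

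**Effect detectable with 80% power.**

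| Alpha per test | 80 evaluable | 60 evaluable |
|---|---|---|
| 0.05 | 0.63 | 0.74 |
| 0.0125 (K = 4) | 0.76 | 0.89 |

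**If Bonferroni is for post hoc contrasts only.** Four independent outcomes at 0.05 each give a family-wise error of 1 − 0.95⁴ = 18.5%. These scores overlap in content and are likely to be positively correlated, so the true figure would be lower.

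**The planned crossover analysis.** For the within-person contrast without carryover, the noncentrality is 0.64 × √N / √(2(1 − ρ)) with N − 2 degrees of freedom, where ρ is the assumed within-person correlation. At K = 4 and ρ = 0:

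- N = 80: noncentrality 4.048, t_crit 2.557, power 93%.
- N = 60: noncentrality 3.505, t_crit 2.578, power 82%.

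At ρ = 0.5 both reach 99% or more.

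**The case against.** The strongest reply is that the Day 21 t-test is a sizing device and not the planned Aim 2 analysis. The crossover model keeps at least about 82% power with four Bonferroni tests and 60 completers, even at zero within-person correlation. ANCOVA at Day 21 also helps: with K = 4 and 30 per group, power is 61% at an assumed baseline correlation of 0.5 and 81% at 0.7. This stands, and it limits the consequence. But the Day 21 figure is the only power the protocol quantifies. The crossover gain needs the absence of carryover, which the protocol itself plans to test. If carryover forces reliance on Period 1, the Day 21 comparison is what remains.

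The retention figure is a benchmark for acceptability, without a time point. Section 4.0 does not expect withdrawals to be common, and imputation is planned. So 30 per group at Day 21 is a pessimistic case and not a forecast. The 62% for four tests needs no loss at all.

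A reader might infer three stronger things that the documents do not support:

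- **That the sample size is miscalculated.** It is not; it reproduces.
- **That power is as low as 30%.** That takes about 14 tests together with the full 25% loss before Day 21. The protocol states no such family. Counting subscales would not settle it either: section 3.6.2 refers to "correlations between the 5 subscales of the MFSI-SF (listed below" and the list that follows shows four.
- **That the statements flatly contradict each other.** The Bonferroni paragraph carries a post hoc label, so its reach is ambiguous. On the narrow reading it can coexist with per-outcome testing at 0.05, but then the .05 does not cover the four outcomes.

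**Conclusion.** The point holds as a mismatch between a correct calculation and the rules around it. The 80% applies only at alpha 0.05 per outcome with 80 evaluable at Day 21. On the assumption of one score per questionnaire, the Day 21 t-test has about 62% power without loss and 47% with a quarter lost before that visit. With two scores it has 72% and 57%, and with loss alone 68%. If Bonferroni does not reach the outcomes, their joint error is about 19% under independence and less under positive correlation.

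Because the family is unstated, no single power figure follows from the protocol. A later analysis plan could define the family, but the power sentence would still be a protocol statement that fits only the unadjusted, loss-free case.

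Severity is moderate. The primary endpoint is feasibility and acceptability, efficacy is secondary, and the planned model would probably recover the power if there is no carryover.

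**What to change.** 1. Name one fatigue score as the lead Aim 2 outcome, tested at 0.05.
2. State which remaining scores form the multiplicity family, and use Holm in place of Bonferroni. Holm gives the same family-wise control and never less power. If the .05 is meant to cover the lead score as well, test the rest only when the lead score is significant.
3. Restate the effect detectable with 80% power for the number evaluable at Day 21: 0.74 with 60 evaluable at alpha 0.05. If Bonferroni over four questionnaires is kept, state 0.76 with 80 evaluable and 0.89 with 60.
4. Add the power of the planned crossover model, with its assumed within-person correlation, the expected loss and the assumption of no carryover.

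This changes protocol and analysis plan wording only and adds no participants. The price is a less favourable stated figure for Day 21.

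### Section 3.6.5 leaves the Day 1 score off its covariate list, and Section 3.7 names change scores beside ANCOVA as a saving although they save patients only if the baseline correlation exceeds 0.5

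*Protocol*

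**What the plan says.** The power paragraph in Section 3.7 rests on a simple comparison, "assuming a two-tailed two-sample t-test on the outcomes at day 21", with a "Type 1 error rate of 0.05". It concludes that "we would need a sample size of 80 to detect an effect size of 0.64". Section 3.1 matches this: "We will enroll 80 eligible CS participants who will be randomized into two groups of 40".

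The paragraph then adds that ANCOVA, or a two-sample t-test on change scores, could do better. In its words, an "independent t-test comparing change scores would be powerful or require less sample size to detect the same effect size depending on the correlation" (Day 1 with follow-up). It gives no value of that correlation and no threshold.

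Section 3.6.5 begins "We will analyze the following covariates to determine effects on outcomes" and lists age, sex, race and time since last treatment. The Day 1 score is not on the list, although Section 3.5 has all four questionnaires completed on Day 1 before the assignment envelope is opened.

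For Specific Aim 2, the Statistical Analysis part of Section 3.7 plans "mixed models repeated measures analysis, such as repeated measures analysis of covariance". It mentions a test for carryover and the use of each patient as his or her own control. It does not say how the Day 1 score enters the model.

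**The concern.** The sentence puts two methods under one qualifier and names only one direction of effect, a saving. That direction is safe for ANCOVA. For change scores it can reverse: below a certain correlation, subtracting the baseline adds more noise than it removes, and the test needs more patients than the plain Day 21 comparison.

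The covariate list is the other half of the point. The Day 1 score of the same scale is measured before randomised treatment, is already in hand, and is the natural covariate for a between-group comparison of the later score. A reader who takes Section 3.6.5 as the full list would leave it out and forgo precision in the between-patient comparisons.

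**Working it through.** **Inputs.** Two-sided alpha 0.05, effect size d = 0.64 and total N = 80 (Section 3.7); 40 per group (Section 3.1). The baseline to follow-up correlation r is not given, so a range is shown. Equal SDs at Day 1 and Day 21 are assumed.

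**The plan's own figure.** For a two-sample t-test the noncentrality is d × √(n/2) = 0.64 × √20 = 2.86 on 78 degrees of freedom, which gives power 0.807. Solving for 80% power gives 39.3, so 40 per arm and 80 in total. The stated N reproduces.

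**Variance factors relative to the raw Day 21 score.**
- Change score: Var(Y − X) = σ² + σ² − 2rσ² = 2(1 − r)σ². The factor 2(1 − r) exceeds 1 whenever r < 0.5.
- ANCOVA on Day 1: residual variance (1 − r²)σ². The factor never exceeds 1.
- Ratio of the two: 2(1 − r)/(1 − r²) = 2/(1 + r). This is above 1 for every r below 1, so ANCOVA is at least as efficient throughout.

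**Power and N.** Replace d by 0.64/√factor and recompute with the noncentral t, ignoring the one degree of freedom that ANCOVA spends. For example, at r = 0.3 the change-score effect is 0.64/√1.40 = 0.541 and the ANCOVA effect is 0.64/√0.91 = 0.671.

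| r | Change: factor | Power at 40/arm | N for 80% | ANCOVA: factor | Power at 40/arm | N for 80% |
|---|---|---|---|---|---|---|
| 0 | 2.00 | 0.516 | 156 | 1.00 | 0.807 | 80 |
| 0.2 | 1.60 | 0.608 | 126 | 0.96 | 0.823 | 76 |
| 0.3 | 1.40 | 0.666 | 110 | 0.91 | 0.842 | 72 |
| 0.4 | 1.20 | 0.733 | 94 | 0.84 | 0.870 | 68 |
| 0.5 | 1.00 | 0.807 | 80 | 0.75 | 0.904 | 60 |
| 0.6 | 0.80 | 0.885 | 64 | 0.64 | 0.942 | 52 |
| 0.7 | 0.60 | 0.954 | 48 | 0.51 | 0.977 | 42 |

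**Where a Day 1 covariate helps in this design.**
- *Within-patient treatment contrast, both periods observed.* The Day 1 score is constant within a patient and cancels from the difference between periods. Simulation of a two-period crossover agrees: the treatment estimate is unchanged and its SE essentially so.
- *Carryover test.* This compares the sum of a patient's two period scores between groups. With a common correlation r among Day 1, Day 21 and Day 49, the sum has variance 2(1 + r)σ² and covariance 2rσ² with Day 1. The adjusted variance is therefore 1 − 2r²/(1 + r) of the unadjusted: 0.86, 0.67 and 0.42 at r = 0.3, 0.5 and 0.7.
- *Patients missing Period 2.* They contribute only between-patient information. At 25% dropout, simulation puts the SE of the treatment effect about 1-3% lower with the covariate.

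**The case against.** The strongest reply is that nothing in the trial depends on the sentence. It is a conditional aside after the sample size has been set. It already says that the gain depends on the correlation, and the planned Aim 2 analysis is a repeated-measures mixed model, not a change-score t-test. All of this stands. A reader might infer that the protocol treats the two methods as interchangeable, or that the trial's power will fall to 61-67%. The text supports neither: it sets the methods side by side without equating them, and the low figures need both an analysis that nobody has planned and an r of about 0.2 to 0.3.

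A reader might also infer that r must be low because entry requires a fatigue score of 4 or more. The documents do not show this. The entry rating is a single 0-10 item that leaves 4 to 10 open, and it is not one of the four outcome questionnaires.

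Nor does the covariate list prove that baseline will go unadjusted. Section 3.6.5 lists demographic and clinical factors to be examined. Section 3.6 counts Day 1 among the four administrations, so it may enter the mixed model as a response. The exact model terms may also sit in an analysis plan that is not shown.

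Finally, the gain in the table does not carry over to the main crossover contrast, as the working shows. What survives is that the sentence's implied saving is wrong for change scores when r is below 0.5, and that naming the Day 1 score is a nearly free gain for the between-patient comparisons.

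**Conclusion.** The point holds in a limited form and is minor. The change-score remark is correct only for r above 0.5, assuming equal SDs. For r from 0.2 to 0.7, a Day 21 comparison at d = 0.64 with 40 per arm has 82-98% power with ANCOVA and 61-95% with change scores. The Day 1 score is missing from the listed covariates although it is collected.

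The stated N of 80 is right for the test it names and does not change. The benefit of the covariate is confined to the Day 21 between-group comparison on which the trial was sized, the carryover test, and, slightly, patients with one period missing. The protocol gives no r, so the size of the benefit can be shown only as a range. Aim 2 is a secondary objective in a pilot whose primary endpoint is feasibility and acceptability, which also keeps the weight of the point low.

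**What to change.** In Section 3.6.5, add the Day 1 score of the same scale as a covariate for the Day 21 between-group comparison and for the carryover test. Include it in the Aim 2 mixed model as well, unless Day 1 is already modelled there as a repeated response, and say which of the two applies.

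In Section 3.7, either delete the change-score remark or state that it saves patients only if r is above 0.5.

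This means one line and one sentence of text, no new data, and one degree of freedom in the analysis.

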**Statistical Analysis**

**Specific Aim 1:** We will evaluate the feasibility of recruiting and enrolling CSs into an OLP intervention.

Feasibility: among eligible CSs who inquire about our study, we will calculate the proportion of those who, after completing the screening procedure,

- sign the consent form;
- decline to participate;
- participate but drop out.

During the screening process, prospective enrollees will be asked 3 questions that pertain to credibility belief, outcome expectancies, and acceptability of an OLP. The rationale for asking these questions is to assess the feasibility of an OLP study for CSs, and whether credibility beliefs, outcome expectancy predict acceptability (which may have implications for selecting patients for future clinical trials). We will use an analysis of variance (ANOVA) to determine if credibility belief and/or outcome expectancy predicts acceptability.

- **Credibility Belief**: “Based on what I have said today, how logical does taking placebo pills to make help someone feel better seem to you?” Responses will range from 0 (makes no sense at all) to 10 (makes perfect sense).
- **Outcome Expectancy**: “At this point, how helpful do you think this treatment will be in reducing your fatigue?” Responses are measured on a 0% to 100% scale.
- **Acceptability**: “Based on my description of the study, are you still interested in participating?” Responses will be “yes” or “no”, or “not sure”. Those who respond “not sure” will be given 48-hours to decide if they wish to participate and will receive a follow-up call.

Acceptability: This will be determined proportionally by:

- **Accrual Rate**: baseline = 80 eligible participants
- **Retention Rate**: baseline = >75%
- **Adherence Rate**: placebo adherence by actual pill count and medication diary entries compared to an anticipated baseline rate of 100%.

For the analysis of acceptability, we will use a chi-square test, or Fisher’s exact test when the assumptions for the chi-square are not tenable. We will also apply log linear models if necessary to adjust for covariates.

**Specific Aim 2:** We will test the hypothesis that an OLP intervention reduces symptoms severity of CRF and improves quality of life for CSs compared to an observational control. The primary analysis for this aim will consist of mixed models repeated measures analysis, such as repeated measures analysis of covariance. This will allow the investigators to properly test for the absence of a carryover effect as well as account for the fact that all patients will receive both treatments (i.e., this type of analysis allows each patient to serve as his/her own control).

**Supplementary Aim:** evaluates the presence or absence of the COMTVal18Met genotype as a correlate for improved fatigue conditions and quality of life. We will measure this using a logistic regression model to determine associations. In addition, we will calculate the odds ratio and corresponding 95% confidence intervals.

**Multiple Comparisons Tests (Post Hoc Test):** To account for multiple comparisons, we will apply a Bonferroni procedure and control the family-wise error rate at .05.

**Missing Data**: Data deemed missing at random (MAR) will be handled using multiple imputation techniques with the Bayesian based Markov-Chain Monte-Carlo (MCMC) method. In supplementary analysis, we will use independent t-tests and chi-square to compare completers versus dropouts.

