**3.2 Participants and Recruitment**

**Participants**: We intend to screen and recruit a sufficient number of individuals in order to enroll 80 cancer survivors, over the age of 19 who received oncology treatments at UAB and who meet our inclusion/exclusion criteria.

**Recruitment:** The primary method for identifying potential participants for this study will be through medical records examination. We will attempt to get a listing of people who were treated for cancer by cancer stage between 2009 – 2016 from the UAB Tumor Registry, the Center for Clinical and Translational Science and IMPACT. We will then compare this record to concurring physician’s patient database and to medical records information contained in IMPACT to identify recruits who meet the inclusion and exclusion criteria.

In order to meet this goal, we will also solicit recruits who received treatment at UAB through the use of flyers, posters and advertisement in UAB newspapers, presentations to local support groups and organizations.

Once we identify a list of prospective participants, we will review the listing with the treating physician. Once the treating physician concurs, we will send the prospective participant a letter signed by both the physician and the PI to offer the opportunity of participating in a study that will test a new, natural, non-pharmaceutical treatment for relieving CRF symptom severity. The letter will contain an opt-out option that instructs recipients to call us if they are not interested and we will remove their name from our list. The letter will also explain that if we do not receive an opt-out call from them within a week, we will call them to explain the study further and invite them to participate. To facilitate recruitment, we plan to inform potential candidates that:

- Each participant will receive the OLP at some point during the 7-week study.
- Free parking will be available to help alleviate the associated costs of participation.
- Each participant completing up 4 study visits will receive up to $75.00 in the form of cash in appreciation for their time and effort.

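### The recruitment part of the primary endpoint is measured on a denominator that starts at screening and does not fit the letter-and-call recruitment route

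*Protocol*

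**What the plan says.** Protocol Section 3.6.4 gives the primary endpoint as "To evaluate the feasibility of recruiting and enrolling CSs into an OLP and the acceptability of CSs of an OLP for the treatment of CRF". It has two parts, recruitment and acceptability.

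For the recruitment part, Section 3.6.1 and the Specific Aim 1 text under Statistical Analysis in Section 3.7 fix the same denominator: "among eligible CSs who inquire about our study, we will calculate the proportion of those who, after completing the screening procedure", followed by three outcomes (consent signed, participation declined, dropped out after joining).

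Section 3.2 describes how people reach screening. "The primary method for identifying potential participants for this study will be through medical records examination". After the treating physician agrees, a letter goes out. "The letter will contain an opt-out option that instructs recipients to call us if they are not interested and we will remove their name" from the list. For the others, "if we do not receive an opt-out call from them within a week, we will call them to explain the study further". Flyers, posters, advertisements and presentations are an additional route.

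The accrual rate in Section 3.7 is set against "baseline = 80 eligible participants", and Section 3.2 plans to "screen and recruit a sufficient number of individuals in order to enroll 80 cancer survivors". Neither section gives an accrual period or a number to be approached. Retention above 75% and pill adherence against 100% are separate targets. Hypothesis 1 in Section 2.0 requires that most of those screened find the open-label placebo (OLP) credible and acceptable, and that the enrollment, retention and adherence targets are met.

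**The concern.** On the main route nobody inquires: the study team makes the contact. Read literally, the denominator describes only the supplementary flyer and advertisement route. Read generously, it means everyone eligible who finishes screening. On either reading, three groups on the main route are lost before counting starts: those who opt out of the letter, those never reached, and those who refuse on the call before screening is complete.

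The accrual measure does not fill the gap. It is called a rate but is a count, and the plan is to approach as many people as it takes.

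Section 1.0 says the pilot should provide feasibility information and lead to a larger trial. That trial needs the yield per patient approached, and the proportions as defined cannot supply it. If opt-outs are not tallied when they occur, the figure may not be recoverable, because their names are removed from the list.

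**Working it through.** **1. The plan's own figure.** Section 3.7 states N = 80 for effect size 0.64, two-sided alpha 0.05 and 80% power. The normal approximation gives 2 × (1.96 + 0.842)² / 0.64² = 38.3, so 39 per arm. The noncentral t gives 39.3, so 40 per arm and 80 in total, with power 80.7%. The figure reproduces. It belongs to the efficacy aim and is not in dispute.

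**2. Overstatement from opt-outs.** The protocol gives no opt-out or eligibility rate, so every rate below is an assumption. Let o be the opt-out share, e_c the eligible share among those called and e_o the eligible share among opt-outs. Suppose that everyone called is screened and all enrollees come through the letter. For L letters:

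- denominator as defined: L(1 − o)e_c
- denominator including eligible opt-outs: L[(1 − o)e_c + o·e_o]
- ratio: 1 + [o/(1 − o)] × (e_o/e_c)

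If e_o = e_c, this reduces to 1/(1 − o):

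- o = 10%: 1/0.9 = 1.11
- o = 30%: 1/0.7 = 1.43
- o = 50%: 1/0.5 = 2.0

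The factor depends on the eligibility assumption. At o = 30% it is 1 + 0.429 × 0.5 = 1.21 if opt-outs are eligible half as often, and 1.00 if none is eligible. Losses from unreached patients push it the other way. With a further 30% lost before screening at equal eligibility, o = 10% gives 1/(0.9 × 0.7) = 1.59.

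**3. Illustration with assumed counts.** Of 300 letters, 90 are answered by an opt-out and 210 patients are called and screened. At 60% eligibility, 126 are eligible and 84 are not; 80 sign and are randomized.

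- Screened-only, as the protocol defines it: 80/126 = 63%
- Opt-outs given the observed 60% eligibility: 80/(126 + 54) = 80/180 = 44%
- Mailed minus known ineligible, so every opt-out counts as eligible: 80/(300 − 84) = 80/216 = 37%

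The 63% would be the same for any number of opt-outs.

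**4. Accrual.** With no limit on approaches, 80 is reached after about 80/0.30 = 267 approaches at 30% uptake, or 80/0.05 = 1600 at 5%. The criterion reads the same in both cases. With a limit it would discriminate: at 10% uptake, the binomial probability of at least 80 is about 0 for 400 approached, 52% for 800 and 99% for 1000.

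**5. Drop-out.** With 20 drop-outs in the same illustration, the Section 3.7 proportion is 20/126 = 16%, while over those enrolled it is 20/80 = 25%.

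**6. The retention target, for contrast.** Retention above 75% needs at least 61 of 80. The probability of passing is 14% at true retention 70%, 46% at 75%, 84% at 80% and 99% at 85%.

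**The case against.** A reader might infer that the primary endpoint can hardly come out negative. The protocol does not support that. The endpoint also covers acceptability, and the retention and adherence targets can fail, as step 6 shows for retention. People who are screened and then decline do count against the consent proportion. Accrual can also fall short: the records pool is finite (patients treated at one centre in 2009–2016, stage II–IV, physician agreement needed), and Section 4.0 has accrual reviewed weekly.

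A reader might also take the 44% in the illustration as refuting the expected majority. It does not. Hypothesis 1 speaks only of those screened, and for acceptability that starting point is defensible. As Section 3.2 describes it, the letter offers a new natural treatment that is not a drug; placebo pills are listed among the points told at telephone screening. An opt-out is evidence about recruitment yield, not necessarily a refusal of OLP.

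The factor 1/(1 − opt-out share) is conditional. Eligibility needs a fatigue rating taken on the call, so it is unknown for opt-outs, and some enrollees may come through flyers or advertisements.

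Nor does the drop-out proportion contradict the retention rate. It has a different denominator, and drop-out among those enrolled follows by division: (20/126)/(80/126) = 25%.

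Finally, participant-flow detail is often left to a statistical analysis plan, and none is shown. That covers the absence of a flow table. It does not cover a denominator that the protocol itself writes twice and that does not match its own recruitment section.

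**Conclusion.** The point holds for the recruitment part of the primary endpoint only. The feasibility proportions are tied to people who inquire and finish screening, while the main route is letter and call, so losses before screening cannot show. The accrual measure is a count without a period or an approached denominator; it could be missed if the pool runs out, but reaching it says little about yield. The acceptability hypothesis and the retention and adherence targets stand.

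The size of the overstatement cannot be determined from the protocol. The range of 1.11 to 2.0 times assumes opt-out shares of 10% to 50%, equal eligibility of opt-outs and those called, letter-only enrollment, and no loss of called patients before screening. It is smaller if opt-outs are less often eligible and larger if many are never reached. This is a cheap improvement that should be made, because it changes what the pilot can conclude about recruiting survivors.

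**What to change.** - In Sections 3.6.1 and 3.7, replace the reference to people who inquire with wording that matches the route in Section 3.2.
- Keep a log, separately for the letter route and for self-referral (flyer, advertisement or presentation), of the numbers mailed or inquiring, opted out, not reached, screened, eligible, consented, randomized and retained. Record a de-identified opt-out count as opt-outs occur.
- For the letter route, report uptake as letter-route randomized / (mailed − known ineligible). Add a sensitivity version that applies the observed eligibility rate to opt-outs and unreached patients, and show both beside the screened-only proportion. Keep self-referred participants out of this numerator, since they are not in its denominator.
- Report accrual as randomized per month and, for the letter route only, per 100 mailed.
- Compute drop-out over randomized participants so that it agrees with the retention rate.

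The cost is a tally of letters and calls that the team already handles, and an uptake figure less favourable than the screened-only one.
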